### Procedure for unblinding if needed {17b}

Data analysis from spreadsheets of random numbers was done to determine the assignment; there is no human involvement; and the process is fully concealed from both study investigators and prospective participants until the study arm is assigned.

## Data collection and management

### Plans for assessment and collection of outcomes {18a}

Software analysis of all the prostheses fabricated by all three ways

### Plans to promote participant retention and complete follow-up {18b}

Not applicable as there are no follow-ups involved in the study. The outcomes will be checked on the day of prosthesis insertion; therefore, adherence to intervention will not be an issue because the patients will be evaluated for primary and secondary outcomes on the day of prosthesis insertion because cranioplasty is an elective surgical procedure carried out for the purpose of improving aesthetics and, in some cases, function. We are using PMMA flaps for cranioplasty procedures which have a complication rate of 9.2–23% (most commonly infection) according to a study by Enrique-Caro-Osiro et al. Further studies have shown a slight decrease in infection rate when performed within 3 months of craniectomy.

### Data management {19}

Electronic data management will be done; the primary investigator will collect the data and will enter the data into the database for screening and randomisation purposes.

### Confidentiality {27}

Personal information about potential and enrolled participants will be collected and maintained in order to protect confidentiality before, during, and after the trial.

### Plans for collection, laboratory evaluation and storage of biological specimens for genetic or molecular analysis in this trial/future use {33}

Not applicable as there is no collection, laboratory evaluation and storage of biological specimens for genetic or molecular analysis in this trial because the procedure of the trial is explained as followsThe impression of the defect will be recorded by Conventional manual method, photogrammetry method, and 3D scanning.The defect will be modelled in three ways: first is as per the manual dimension taken on the patient, second is organisation of photographic image taken with lab standards and third is plotting of point cloud data to generate the virtual 3D model.For photogrammetric prosthesis design: finite photos/images will be taken at multiple angles to model the 3D virtual design. With the use of minimum photographs, the 3D modelling can be performed by using freeware, and a mould is obtained.The CAD software was used to design the prosthesis, and the final negative mould can be printed using additive manufacturing.The mould fabricated by all three methods will be analysed by a software using reverse engineering technology

Clearly, biological specimens will not be collected, so this field is not applicable.

## Statistical methods

### Statistical methods for primary and secondary outcomes {20a}

Analytical tests like chi-square test and Student’s *t*-test will be performed. All the statistical analysis will be performed; *p* 0.05 will be considered as the level of significance.

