### Sample size {14}

45 Daniel formula for sample size calculation$$n=\frac{Za/{2}^2\cdot P\cdot \left(1-P\right)}{d^2}$$where*Zα*/2^2^ is the level of significanceAt 5%, i.e. 95% confidence interval = 1.96*P* = prevalence of craniomaxillofacial defects = 3% = 0.03*d* = desired error of margin = 5% = 0.05$$n=\frac{1.96^2\times 0.03\times \left(1-0.03\right)}{0.05^2}=44.71$$*n* = 45 patients needed for the study

Study reference: Mohamed Khallaf et al.

Formula reference: Daniel et al.

Statistical method: chi-square test, one-way ANOVA, Tukey multiple comparison test

Software used: SPSS 27.0 V and Graph Pad Prism 7.0V

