### Methods for additional analyses (e.g. subgroup analyses) {20b}

#### SPIRIT guidance: methods for any additional analyses (e.g. subgroup and adjusted analyses)

As there are no subgroups in the study, the subgroup analysis will not be carried out. The population will be studied under three groups—conventional impression, 3D scanning, and photogrammetry—so there is no role of subgroups.

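### Sections {20a} and {14} name different tests for the same three-group comparison; unadjusted pairwise t-tests under {20a} would carry a family-wise error of about 9% to 12% instead of 5%

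*Protocol article*

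**What the plan says.** The protocol article describes the analysis in two places.

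- *Statistical methods for primary and secondary outcomes {20a}*: "Analytical tests like chi-square test and Student’s *t*-test will be performed". The section then says that a p-value of 0.05 "will be considered as the level of significance". It mentions neither ANOVA nor a multiplicity adjustment.
- *Sample size {14}*, below the formula: "Statistical method: chi-square test, one-way ANOVA, Tukey multiple comparison test".

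Three groups are to be compared. The section on additional analyses {20b} says "The population will be studied under three groups", naming conventional impression, 3D scanning and photogrammetry. The last item under Objectives {7} is a comparison of the accuracy of all three methods. The choice of comparators {6b} is narrower and sets photogrammetry against the other two. No section names one primary pair, says which test applies to which outcome, or reconciles {20a} with {14}.

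**The concern.** Both statements are current text and cover the same continuous outcomes. Student's t-test handles two groups at a time, so using it with three groups means two or three tests per outcome, each judged at 0.05 unless something more is said. Tukey's procedure keeps the chance of any false positive across the three pairs at 5%. The two sections can therefore lead to different conclusions from the same data.

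The Outcomes section {12} expects the study to point to the best of the three methods. Error control across pairs matters for that kind of claim. While the document supports both analyses, the choice can be made once the results are known, and an analyst could cite the protocol for either.

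**Working it through.** **Inputs**

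- Groups: 3, hence 3 possible pairs ({20b}, Objectives {7}), or 2 pairs if only photogrammetry is compared with each of the others ({6b}).
- Significance level: 0.05 ({20a}). Sidedness is not stated; two-sided is assumed.
- Total sample size: 45 ({14}). The allocation ratio is not stated; 15 per arm is assumed, with 12/15/18 as a check.
- Outcome: one continuous, normally distributed measure with equal variances (assumed).

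**The plan's own figure**

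n = 1.96² × 0.03 × 0.97 / 0.05² = 44.716, rounded up to 45. The protocol's 44.71 and 45 are reproduced. This is a precision formula for a single prevalence. It uses neither the t-test nor ANOVA, so it cannot show which analysis was intended.

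**Family-wise error when no method differs (15 per arm)**

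With one pooled error term on 42 degrees of freedom, the chance that at least one of three unadjusted t-tests is significant is the upper tail of the studentized range: P(Q(3, 42) > √2 × t(0.975, 42)) = 12.0%.

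Simulation of 400,000 null trials with separate two-sample t-tests (28 degrees of freedom each) gives:

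| Procedure at 0.05 | Chance of at least one false positive |
|---|---|
| Three unadjusted t-tests | 12.2% |
| Two unadjusted t-tests (photogrammetry against each other method) | 9.0% |
| One-way ANOVA F-test | 5.0% |
| Tukey, all three pairs | 4.9% |

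The ratios to 5% are 12.2 / 5.0 = 2.4 for three pairs and 9.0 / 5.0 = 1.8 for two.

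**Sensitivity**

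- Arms of 12/15/18: 12.3% for three pairs and 8.9% for two.
- Every patient measured by all three methods, with paired t-tests: 12.2% with 45 patients, 12.4% with 15.
- The independence formula, 1 − 0.95³ = 14.3%, overstates the figure because the pairs share groups.

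**How often the two sections would disagree**

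In about 7% of null trials (15 per arm), at least one of the three t-tests is significant while Tukey finds no pair significant. This agrees with the difference between the rates above: 12.2% − 4.9% = 7.3%.

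**Price of adjustment**

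The critical values are t(0.975, 28) = 2.048 and q(0.95; 3, 42)/√2 = 2.429. The standard error of a pairwise difference, in SD units, is √(2/15) = 0.365. From the noncentral t distribution, 80% power for one pair is reached at 1.06 SD with the t-test and at 1.20 SD with Tukey.

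**The case against.** Four points can fairly be made in defence of the plan.

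- *The list in {20a} is illustrative.* It introduces its tests as examples and does not exclude ANOVA, and multiplicity detail is often left to a statistical analysis plan that is not shown here. This stands: the document does not commit the trial to unadjusted t-tests. It does not remove the conflict, because a reader still cannot tell which test decides significance.
- *The sections could be read together.* If t-tests were run only after a significant ANOVA, the family-wise error with exactly three groups would stay at 5.0% (simulated, 15 per arm). This is correct, so naming a t-test does not by itself break the 5% level. But no section describes such a sequence, and {14} names Tukey as the follow-up to ANOVA.
- *Only two pairs may be intended.* The comparator section {6b} supports this, and the error is then 9.0%. The Objectives support three pairs. Both readings are open, so a range is given.
- *Tukey is not the only valid choice.* Holm, Bonferroni or gated t-tests would also control the error. This stands, and the fix allows for it.

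A reader might also infer from the two critical values that every pair with a t statistic between 2.05 and 2.43 is significant under {20a} and not under {14}. That does not follow: the two-sample t uses the variance of two arms and Tukey that of all three. In null simulations about 9% of pairs in that band were significant by Tukey. The 7% disagreement rate takes this into account.

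**Conclusion.** The contradiction holds. The section that governs the analysis names a two-group test for a three-group trial, another section names a suitable three-group analysis, and nothing reconciles them.

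The size is conditional. If {20a} is followed with unadjusted pairwise t-tests, the family-wise error for one continuous outcome is about 12% with all three pairs tested and about 9% with two, against 5% for ANOVA or Tukey. This assumes two-sided tests, normal data with equal variances, and 15 per arm; the three-pair figure barely moves with unequal arms or paired data.

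A reader might infer that the plan as written more than doubles the false-positive rate. The document does not support that without conditions. It takes all three pairs, no adjustment and no preceding ANOVA, none of which {20a} states; with two pairs the ratio is 1.8. Each single t-test also keeps its own 5% level.

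**What to change.** In {20a}, replace Student's t-test with the analysis already named in {14}: for continuous outcomes, one-way ANOVA with Tukey-adjusted pairwise differences and 95% confidence intervals, at a family-wise two-sided level of 5%. Another procedure that controls multiplicity is equally acceptable if it is named and the pairs it covers are listed. If every patient receives all three methods, use a patient-level model for the same adjusted comparisons, because independent-groups ANOVA would then be unsuitable. Keep the chi-square test for categorical outcomes. Replace the list of tests in {14} with a reference to {20a}, so that the analysis is stated once. Make the change before any outcome data are analysed.

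The cost is wording, plus some power: at 15 per arm the pairwise difference detectable with 80% power rises from about 1.06 to 1.20 SD.

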### Interim analyses {21b}

Not applicable as we are inserting the prosthesis on the day of surgery, so interim analysis is not required; the outcomes will be checked on the day of prosthesis insertion; therefore, adherence to intervention will not be an issue because the patients will be evaluated for primary and secondary outcomes on the day of prosthesis insertion because cranioplasty is an elective surgical procedure carried out for the purpose of improving aesthetics and, in some cases, function.

### Methods for additional analyses (e.g. subgroup analyses) {20b}

#### SPIRIT guidance: methods for any additional analyses (e.g. subgroup and adjusted analyses)

As there are no subgroups in the study, the subgroup analysis will not be carried out. The population will be studied under three groups—conventional impression, 3D scanning, and photogrammetry—so there is no role of subgroups.

### Methods in analysis to handle protocol non-adherence and any statistical methods to handle missing data {20c}

NA

As noted above in the additional analysis, a secondary, per-protocol analysis will examine outcomes by whether or not the participant was engaged in shared decision-making, as reported by clinicians and judged by study staff, regardless of whether the decision aid was used.

Missing data will be described, and, if extensive, limitations will be identified in our discussion. We will compute standardised effect sizes to help determine the degree of imbalance on baseline characteristics and subsequently inform multivariable model development.

### Plans to give access to the full protocol, participant level-data and statistical code {31c}

The datasets analysed during the current study and statistical code are available from the corresponding author on reasonable request, as is the full protocol.

## Oversight and monitoring

### Composition of the coordinating Centre and trial steering committee {5d}

The committee consist of the following:The head of the department of prosthodonticsP.G. guideResearch scientistPrincipal investigatorSurgeonStatisticianData manager

### Composition of the data monitoring committee, its role and reporting structure {21a}

Composition of data monitoring committee (DMC) is as follows: research in charge of the institute and research in charge of the department.

### Adverse event reporting and harms {22}

Data will be collected, assessed, and spontaneously reported during adverse events and other unintended effects of trial interventions or trial conduct.

### Frequency and plans for auditing trial conduct {23}

The project management group meet will review the trial conducted every month. The trial steering group and the independent data monitoring and ethics committee meet will review and conduct the trial period till the trial is complete.

### Plans for communicating important protocol amendments to relevant parties (e.g. trial participants, ethical committees) {25}

The sponsor and funder will be notified first; then, the PI will notify the centres, and a copy of the revised protocol will be sent to the PI to add to the Investigator Site File.

### Dissemination plans {31a}

Publication

## Trial status

[ref no: DMIMSU(DU)/IEC/2022/781] protocol version number 1; recruitment began on September 2022 and approximately will be completed by January 2024.

## Data Availability

Access to investigator
